# Neoadjuvant therapy of sequential TACE, camrelizumab, and apatinib for single huge hepatocellular carcinoma (NEO-START): study protocol for a randomized controlled trial

**DOI:** 10.1186/s13063-024-08340-1

**Published:** 2024-07-19

**Keywords:** Hepatocellular carcinoma, Neoadjuvant therapy, Camrelizumab, Apatinib, Transarterial chemoembolization

## Abstract

**Background:**

The high recurrence rate after liver resection emphasizes the urgent need for neoadjuvant therapy in hepatocellular carcinoma (HCC) to enhance the overall prognosis for patients. Immune checkpoint inhibitors, camrelizumab combined with an anti-angiogenic tyrosine kinase inhibitor (TKI) apatinib, have emerged as a first-line treatment option for patients with unresectable HCC, yet its neoadjuvant application in combination with transarterial chemoembolization (TACE) in HCC remains unexplored. Therefore, this study aims to investigate the efficacy and safety of sequential TACE, camrelizumab, and apatinib as a neoadjuvant therapy for single, huge HCC.

**Methods:**

This multi-center, open-label randomized phase 3 trial will be conducted at 7 tertiary hospitals. Patients with single huge (≥ 10 cm in diameter), resectable HCC will be randomly assigned in a 1:1 ratio to arm of surgery alone or arm of neoadjuvant therapy followed by surgery. In the neoadjuvant therapy group, patients will receive TACE within 1 week after randomization, followed by camrelizumab (200 mg q2w, 4 cycles), along with apatinib (250 mg qd, 2 months). Patients will receive liver resection after neoadjuvant therapy unless the disease is assessed as progressive. The primary outcome is recurrence-free survival (RFS) at 1 year. The planned sample size of 60 patients will be calculated to permit the accumulation of sufficient RFS events in 1 year to achieve 80% power for the RFS primary endpoint.

**Discussion:**

Synergistic effects provided by multimodality therapy of locoregional treatment, TKI, and anti-programmed cell death 1 inhibitor significantly improved overall survival for patients with unresectable HCC. Our trial will investigate the efficacy and safety of the triple combination of TACE, camrelizumab, and apatinib as a neoadjuvant strategy for huge, resectable HCC.

**Trial registration:**

www.chitr.org.cn ChiCTR2300078086. Registered on November 28, 2023. Start recruitment: 1st January 2024. Expected completion of recruitment: 15th June 2025.

## Introduction

### Background and rationale {6a}

Hepatocellular carcinoma (HCC) is one of the most prevalent and deadly cancers globally, especially in China, where HCC stands as the second most prominent contributor to cancer-related fatalities [1, 2]. It is generally accepted that complete extirpation of the tumor provides the best opportunity for a cure and offers a favorable overall survival (OS) for patients with resectable HCC [3–5]. However, HCC is considered a difficult disease to cure due to its high recurrence rate after surgery, which is believed to be associated with the liver microenvironment [6]. Effective and well-tolerated neoadjuvant therapies are urgently needed to prevent postoperative recurrence in order to improve the overall prognosis of patients with HCC.

Neoadjuvant therapy is commonly used for patients with malignancies to stage down advanced disease and reduce postoperative complications, however, there is insufficient research support and limited endorsement in major guidelines for neoadjuvant treatments for HCC [7]. It remains controversial whether transarterial chemoembolization (TACE), a potential neoadjuvant locoregional therapy for HCC, could reduce tumor recurrence and prolong survival or not. Results from some studies showed that neoadjuvant TACE did not improve surgical outcomes for resectable HCC [8]. Conversely, results from some other studies showed neoadjuvant TACE was associated with improved OS and recurrence-free survival (RFS) for huge HCC (≥ 10 cm) [9, 10]. On the other side, neoadjuvant TACE, inducing partial tumor necrosis, may result in less secure attachment of residual tumor cells, making them more prone to dislocation into the bloodstream during liver resection [8].

Tyrosine kinase inhibitors (TKIs) and immune checkpoint inhibitors (ICIs) are now commonly used as systemic therapy for HCC patients, which are also being incorporated into neoadjuvant treatments. Earlier research indicated that the combination of TKI and ICI produced a synergistic antitumor effect, concurrently promoting tumor immune stimulation and vascular remodeling [11, 12]. In the latest phase III clinical trial, the combination of camrelizumab and apatinib as a first-line treatment for unresectable HCC demonstrated a median OS time of up to 22.1 months with an objective response rate (ORR) of up to 34.3% [13]. This combination has also shown promising outcomes in neoadjuvant therapy. In a phase II trial, 94.4% of patients with Barcelona Clinic Liver Cancer (BCLC) B/C stage HCC successfully underwent surgery after neoadjuvant therapy of camrelizumab plus apatinib, with a 1-year RFS rate reaching 53.85% [14]. Besides, several studies showed the combination of locoregional and systematic treatments could significantly improve tumor response and OS for patients with advanced HCC [15–17]. Our prior study evaluated the safety and efficacy of a triple combination of TKI, TACE, and anti-PD-1 inhibitors for patients with unresectable HCC, and promising results were found [18]. Inspired by this, we tried to extend the use of the triple combination to adjuvant and neoadjuvant settings. A phase II trial of adjuvant therapy was initiated to investigate the efficacy of the triple combination in patients with a high risk of HCC recurrence after surgery [19]. Here, we designed a prospective, open-label, randomized phase 3 trial to investigate the efficacy of neoadjuvant therapy of sequential TACE, camrelizumab, and apatinib for a single huge HCC.

### Objectives {7}

The study aims to (1) directly compare the efficacy of neoadjuvant therapy followed by surgery and surgery alone on HCC recurrence risk and survival in patients with single huge HCC; (2) explore the safety of neoadjuvant therapy regimen of TACE, camrelizumab, and apatinib; and (3) offer evidence and guidance for neoadjuvant therapy strategy in HCC patients with a high risk of recurrence.

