### Outcomes {12}

The primary endpoint is the 1-year RFS rate, defined as the time period from randomization to the first documented HCC recurrence or death from any cause. The key secondary endpoints include pathological remission degree and OS which was defined as the time period from randomization to death from any cause. Pathological complete remission (pCR) is defined as existent ≤ 1% active tumor cells, while major pathological remission (mPR) is defined as ≤10% active tumor cells. Safety outcomes encompass adverse events (AEs), defined as the occurrence of ≥ 3 grade hematological or non-hematological toxicities (including but not limited to liver dysfunction, hematological abnormalities, hypertension, diarrhea, proteinuria, hand-foot syndrome, etc.). The severity of adverse events will be graded according to the Common Terminology Criteria for Adverse Events (CTCAE v5.0).

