### Sample size {14}

The sample size was performed using the software PASS (version 2015). The calculation is based on the primary endpoint which is RFS in the present study. Previous research data showed that the 1-year RFS rate was 40% for patients with a single huge HCC after surgery [9]. Our prior study showed that the 1-year event-free survival (EFS) rate was 65% for patients with unresectable HCC after receiving a similar treatment regime [22]. Therefore, we hypothesize that neoadjuvant therapy could increase the 1-year RFS rate to 70% for patients with a single huge HCC. Using an alpha of 0.025 at one-sided, a power of 80%, a total of 60 participants needed to be enrolled with 30 in each arm when considering an attrition rate of 10% and an anticipated recruitment period of 1.5 years.

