### Recruitment {15}

We aim to enroll a total of 60 participants across seven hospitals. To achieve this, monthly online conferences are scheduled to monitor enrollment progress at each hospital and strategize methods to accelerate recruitment. Participants at each center will be contacted via telephone. All seven centers are expected to collectively recruit approximately 3–4 participants per month, with an anticipated recruitment period of 1.5 years. The study will run from January 2024 to June 2026.

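### Table 1 schedules no recurrence or survival assessment after Month 12, yet 60 patients approach the stated 80% power only if follow-up runs on to June 2026

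*Protocol article*

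**What the plan says.** Objectives {7} sets out to compare the two strategies "on HCC recurrence risk and survival in patients with single huge HCC". Outcomes {12} adds: "The key secondary endpoints include pathological remission degree and OS". OS is timed from randomization to death, and no horizon is given. Statistical methods {20a} analyses RFS and OS by Kaplan-Meier and Cox models.

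The last column of Table 1 is Month 12. The final marks for living state, primary endpoint and secondary endpoint stand there.

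Recruitment {15} says: "The study will run from January 2024 to June 2026". Trial status expects recruitment to finish before 15 June 2025. June 2026 is therefore about Month 12 for the last patient and about Month 30 for the first.

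On the primary endpoint, the abstract says "The primary outcome is recurrence-free survival (RFS) at 1 year" and that the sample size is meant to "permit the accumulation of sufficient RFS events in 1 year to achieve 80% power for the RFS primary endpoint". Sample size {14} rests on prior data that "the 1-year RFS rate was 40% for patients with a single huge HCC after surgery", a hypothesised 70% with neoadjuvant therapy, one-sided alpha 0.025, 80% power, 10% attrition, 1.5 years of recruitment and 60 patients.

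**The concern.** Two things hang on whether observation stops at Month 12.

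The first is information. OS is analysed as a time-to-event endpoint, but on the printed schedule each patient contributes at most 12 months. Up to about 18 further months on the earliest patients, inside the stated study dates, would not be collected under the trial's schedule. The same holds for RFS events, on which the power depends.

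The second is interpretation. RFS runs from randomization. Controls are to be resected within a week. The neoadjuvant arm is resected after two months of apatinib and an assessment 14 ± 7 days after the last dose, so roughly in Weeks 10–13 (inferred from Intervention description {11a}). At Month 12 the arms have had unequal time since resection, and part of any 1-year difference could be recurrence that comes later rather than recurrence that is prevented.

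**Working it through.** **Inputs from the article.** 1-year RFS 40% vs 70%; one-sided alpha 0.025; power 80%; 30 per arm; accrual 1.5 years; study length about 2.5 years; attrition 10%. **Assumptions.** Exponential times, uniform accrual, attrition (where used) as 10% loss per year. The OS rates are also assumed.

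**1. Events needed for RFS.** Hazards per year are −ln 0.4 = 0.916 and −ln 0.7 = 0.357, so HR = 0.389 and ln HR = −0.944. Schoenfeld: d = 4(1.960 + 0.842)²/0.944² = 35.3 events.

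**2. Reproducing 60.** With follow-up to a common close at 2.5 years, the event probability is p = 1 − [exp(−λ·1.0) − exp(−λ·2.5)]/(1.5λ).
- Control: 1 − (0.400 − 0.101)/1.374 = 0.783.
- Neoadjuvant: 1 − (0.700 − 0.410)/0.535 = 0.458.
- Mean 0.620, so N = 35.3/0.620 = 57 without loss. With loss the mean is 0.576 and N = 61.

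With each patient stopped at Month 12 the mean is (0.60 + 0.30)/2 = 0.45, so N = 35.3/0.45 = 78 without loss and 82 with it. The stated 60 lies close to the first pair and far from the second.

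**3. Power with 60 patients.** Power = Φ(√d/2 × 0.944 − 1.960).

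| Follow-up | Loss | RFS events | Formula | Simulated log-rank |
|---|---|---|---|---|
| Stops at Month 12 | none | 27.0 | 69% | 67% |
| Stops at Month 12 | 10%/year | 25.8 | 67% | 65% |
| To June 2026 | none | 37.2 | 82% | 81% |
| To June 2026 | 10%/year | 34.6 | 79% | 78.5% |

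The longer follow-up helps only a log-rank or Cox comparison. A comparison of the two 1-year rates does not gain from it. With 30 per arm its power is Φ(0.30/√[(0.24 + 0.21)/30] − 1.960) = Φ(0.49) = 69%, or 65% with a pooled variance under the null.

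**4. OS.** Expected deaths, 30 per arm, OS HR 0.6, no loss. The CI factor is exp(1.96 × 2/√deaths).

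| Assumed control 1-year OS | Deaths by Month 12 | Deaths by June 2026 | 95% CI factor |
|---|---|---|---|
| 60% | 19.9 | 29.7 | 2.4 → 2.1 |
| 70% | 14.8 | 23.0 | 2.8 → 2.3 |
| 80% | 9.8 | 15.8 | 3.5 → 2.7 |
| 90% | 4.8 | 8.2 | 5.9 → 3.9 |

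Deaths rise about 1.5- to 1.7-fold. The only OS figure in the article, a 22.1-month median in unresectable disease, corresponds to 1-year OS of 0.5^(12/22.1) = 69%. That gives 15.5 deaths against 24.0. For scale, an OS HR of 0.5 at 80% power needs 66 deaths, more than the patients enrolled.

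**5. Delay alone.** Take the control hazard of 0.916 from resection onward in both arms, no events before surgery, and resection at Week 1 vs Weeks 10–13.
- Month 12: exp(−0.916 × 51/52) = 41% vs exp(−0.916 × 42/52) = 48% to exp(−0.916 × 39/52) = 50%, a gap of 7–10 points with no treatment effect.
- Month 24: 16% vs 19–20%, a gap of 3–4 points.
- With a falling hazard (Weibull shape 0.7) the gaps are about 5–7 and 2–3 points.

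**6. Patients who could reach Month 24.** They must enrol at least 24 months before a close-out at Month 30, so in the first 6 of about 18 recruitment months: 60 × 6/18 = 20.

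**The case against.** No sentence says that follow-up stops at Month 12 or that later data are dropped. OS has no horizon, and Kaplan-Meier and Cox methods use all available time. The interim analysis is set by calendar, 6 months after the last enrolment, when the earliest patients would be near Month 23. A condensed article may leave long-term contact schedules to the full protocol. The near-match of 60 with follow-up to June 2026 suggests that longer follow-up may have been intended. All of this stands, so a reader who infers that later data will be discarded goes further than the text. The study dates do not contradict Table 1 either, since June 2026 is the last patient's Month 12.

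But nothing in the article schedules the longer follow-up. The printed schedule ends at Month 12, the abstract counts RFS events within 1 year, and the only later follow-up named is post-trial care in {30}, tied to no endpoint. The match with 60 is not proof of intent: dividing 57 by 0.9 gives 64, and the Lachin-Foulkes formula gives 63 without loss and 68 with it.

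It is also fair to say that longer follow-up does not rescue OS. At 80% control 1-year OS, an estimated HR of 0.6 would have an interval of about 0.17–2.1 at Month 12 and 0.22–1.6 at close-out. The main cause is 60 patients, a limitation the authors acknowledge. Finally, the delay calculation assumes no events before surgery, so 7–10 points is an upper figure.

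**Conclusion.** The point holds as a mismatch between schedule and power, and as information lost if the schedule is followed literally. With 60 patients the RFS hazard-ratio comparison has about 27 events and 65–69% power at a Month 12 stop, against about 37 events (35 with loss) and 78–82% to June 2026. The stated 80% is approached only with follow-up that Table 1 does not show. These figures rest on constant hazards, uniform accrual and the article's 40% and 70%.

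For OS the gain is about 1.5- to 1.7-fold more deaths, roughly 5–20 becoming 8–30, on assumed survival rates. Two stronger readings are not supported. One is that OS rests on only a handful of deaths: that needs 1-year OS of about 85–90%, which the article does not give. The other is that data past Month 12 would settle whether recurrence is prevented or postponed: only about 20 patients could reach Month 24, about 10 per arm, with fewer than 2 controls expected to be recurrence-free at 16%.

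This should be changed. It does not invalidate the trial.

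**What to change.** Keep the 1-year RFS figure. In Table 1 and Outcomes {12}, state that recurrence and survival status are collected for every randomized patient to a common close-out in June 2026 (minimum about 12, maximum about 30 months). Analyse OS and the RFS hazard ratio on all of that follow-up, and say that the 80% power belongs to the hazard-ratio comparison. Amend the abstract's statement that events accumulate within 1 year to match. If follow-up really ends at Month 12, leave the schedule and restate the power as about 65–69%.

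Label OS as estimation only: hazard ratio and confidence interval, with no claim of benefit or of no difference. Report RFS beyond Month 12 descriptively. Note that unequal time since resection could alone give a 1-year gap of up to about 7–10 points under a constant hazard with no pre-operative events. Do not make persistent separation a test, because too few patients reach Month 24.

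The cost is a protocol amendment and modest status checks for earlier enrollees, with no extra patients and no change to the stated study dates.

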### Trial design {8}

The study is a prospective, multicenter, open-label, randomized controlled trial. Patients will be randomly assigned in a 1:1 ratio to either the experimental group (surgery after neoadjuvant treatment with TACE combined with camrelizumab and apatinib) or the control group (surgical resection without neoadjuvant treatment), using a parallel design with superiority.

## Methods: participants, interventions, and outcomes

### Study setting {9}

From January 2024 to June 2025, patients with single huge (≥ 10 cm in diameter) resectable HCC that are scheduled for liver resection will be screened for eligibility for this trial. Participant recruitment will be conducted at seven hospitals in Sichuan Province, including six general hospitals (West China Hospital, Sichuan Provincial People’s Hospital, Yibin Second People’s Hospital, Neijiang First People’s Hospital, Affiliated Hospital of Southwest Medical University, and Chengdu Third People’s Hospital) and one hospital specialized in oncology (Sichuan Cancer Hospital). All these hospitals are registered with the China National Medical Products Administration for conducting clinical trials. These hospitals are major healthcare institutions in southwestern China, thus patients enrolled represent to some extent the patient population of the region.

### Eligibility criteria {10}

#### Inclusion criteria

(1) Aged between 18 and 75 years old; (2) newly diagnosed with HCC following clinical diagnosis criteria of the American Association for the Study of Liver Diseases (AASLD) [20]; (3) single huge (≥ 10 cm in diameter) tumor without vascular invasion or extrahepatic metastasis; (4) adequate future liver remnnt (FLR) (for patients with liver cirrhosis, FLR more 40% of standard liver volume, for patients without cirrhosis, FLR more than 30% of standard liver volume); (5) adequate liver function: Child-Pugh A grade and indocyanine green retention test at 15 min (ICG-R15) < 20%; (6) adequate hematologic and vital organ function defined by laboratory test results obtained within 7 days before treatment; (7) for patients with hepatitis B virus (HBV) infection, HBV DNA < 2000 IU/ml during screening, initiation of anti-HBV therapy at least 14 days prior to neoadjuvant therapy and willingness to continue anti-HBV; (8) Eastern Cooperative Oncology Group (ECOG) performance status (PS) score ≤ 1.

#### Exclusion criteria

(1) Known cases of fibrolamellar HCC, sarcomatoid HCC, or mixed cholangiocarcinoma and HCC; (2) human immunodeficiency virus infection or autoimmune diseases; (3) a history of severe allergies to any monoclonal antibodies or investigational drug components; (4) currently participating in other clinical trials, or less than 30 days since the end of treatment with an investigational drug in a previous clinical study; (5) pregnant or lactating women; (6) other factors that could potentially affect study outcomes or lead to its early termination (alcohol, drug abuse, serious medical condition, etc.)

#### Criteria for study centers

(1) Academic hospitals with the availability of skilled in liver surgery, TACE, and systemic therapy for liver cancer; (2) desire and capacity to participate in the trial;

### Who will take informed consent? {26a}

Trained researchers will provide detailed study information, including design, aspects, benefits, and potential harms, to potential participants before enrollment.

### Additional consent provisions for collection and use of participant data and biological specimens {26b}

Enrolled participants will sign written informed consent, including the consent for collection and use of biological specimens, ensuring confidentiality of personal information.

## Interventions

### Explanation for the choice of comparators {6b}

Participants allocated to the arm of surgery alone will receive liver resection within 1 week after randomization according to existing guidelines [20]. We will collect the perioperative and follow-up data of participants allocated to the arm of surgery alone.

### Intervention description {11a}

Patients in the control arm will undergo liver resection within 1 week after randomization. Patients in the arm of neoadjuvant therapy will receive TACE within 1 week after randomization, followed by camrelizumab (200 mg q2w, for 4 cycles). They were also given oral apatinib mesylate tablets (250 mg qd, for 2 months). Patients must undergo imaging tests, including computed tomography (CT) scans of the chest/abdomen/pelvis, within 28 days before their first dose of medication. Additional scans of other body areas may be conducted if clinically necessary. After neoadjuvant therapy, a preoperative assessment including a CT scan will be conducted within 14 days (± 7 days) after the last dose of medication. Patients will receive surgery after neoadjuvant therapy if the disease is not assessed as progressive disease. To ensure the safety of the surgery, camrelizumab is discontinued for at least 2 weeks, while apatinib is discontinued for at least 1 week before the surgery.

All TACE procedures were performed by experienced physicians and a uniform treatment protocol was applied to each patient [21]. TACE was performed through the right femoral artery with local anesthesia. After arteriography of the celiac trunk and superior mesenteric artery to visualize arterial vascularization of the liver, body surface-dependent doses of the chemotherapeutic agents 5-fuorouracil (800~1000 mg) and epirubicin-adriamycin (30~40 mg) were injected. Subsequently, lipiodol and polyvinyl alcohol foam embolization particles were injected as selectively as possible into the hepatic segmental artery at the target tumor location. The embolization agent doses ranged from 5 to 30mL and were determined based on the tumor location, size, and number.

The dosages of apatinib and camrelizumab in this study will be selected based on recommended dosages in their drug labels and prior clinical studies for unresectable HCC [13].

### Criteria for discontinuing or modifying allocated interventions {11b}

Discontinuation or modifying of the allocated intervention is possible after a participant withdraws from the intervention and/or trial or based on clinical judgment by the intervention facilitator, e.g., when a participant is unable to continue due to adverse event (AE) caused by camrelizumab and/or apatinib.

### Strategies to improve adherence to interventions {11c}

Several strategies to improve adherence to interventions. Firstly, potential participants are informed of the potential benefits of neoadjuvant therapy based on present evidence. Secondly, potential participants are also informed of specific dates, cycles, and sites of intervention before they decide to participate in this trial. Thirdly, the trial covers the costs of medication, including camrelizumab and apatinib for neoadjuvant therapy. Fourthly, investigators and coordinators of the trial will schedule individual calls with each participant.

